#### Procedure for unblinding if needed {17b}

Not applicable. According to the TwiCs design, patients in the control group will not be informed about their role as a control in this trial.

### Data collection and management

#### Plans for assessment and collection of outcomes {18a}

According to the TwiCs design, demographic and clinical data and regular PROMs collected in the PRESENT cohort will be used for effect estimation. In general, patients fill out the EORTC QLQ-C15-PAL, the EORTC QLQ-BM22, the EuroQol (EQ) 5D-5L, and the BPI at baseline (upon cohort enrolment, i.e., before the start of treatment), 4 and 8 weeks, 3 and 6 months after initial treatment, and every 6 months thereafter. At 2 and 6 weeks, patients fill out an additional BPI [1, 14–18, 23]. Patients can choose to fill out the questionnaires on paper or online.

The primary outcome is physical functioning at 4 weeks that will be assessed using the EORTC QLQ-C15-PAL, a 15-item HRQOL questionnaire representing overall QOL, two functional scales (physical and emotional functioning), and six symptom scales (nausea, loss of appetite, dyspnea, constipation, sleeping difficulties, and fatigue) [14]. Secondary, change in HRQOL from baseline to 4 and 8 weeks and 3 and 6 months will be measured using the EORTC QLQ-C15 (overall QOL, physical and emotional functioning) and EORTC QLQ-BM22 (functional interference and psychosocial aspects). The EORTC QLQ-BM22 is a 22-item questionnaire representing four domains: painful sites, pain characteristic, functional interference, and psychosocial aspects [17, 18]. Items of the EORTC QLQ-C15 and -BM22 will be rated on a Likert scale ranging from 1 (not at all) to 4 (very much) with the exception of the overall QOL item that will be rated on a 7-point Likert scale ranging from 1 (very poor) to 7 (excellent). Scale scores will be linearly transformed to a 0–100 scale where a higher score on the overall QOL and functioning scales indicates better functioning, and on the symptom scales an increase of symptoms. The EORTC QLQ-C15 and -BM22 has been validated in patients with painful bone metastases or advanced cancer [17, 18, 24].

The duration of pain relief up to three months will be measured by the BPI which is a multidimensional tool to evaluate cancer pain [15, 16]. The BPI consists of eleven items representing two domains: pain perception and interference by pain. Items can be rated using a scale from 0 (no pain/interference) to 10 (maximum pain/interference). The BPI has been validated in patients with painful bone metastases [16]. Duration of pain relief will be defined as the time between response and progression or end of follow-up.

Pain response at 2, 4, 6, and 8 weeks and 3 months is defined as [1] a decline in worst pain score of at least two points on an NRS of ten at the treated site without increase in analgesic use or [2] an analgesic decrease of at least 25% without an increase in pain score [25–27]. Worst pain score will be measured with the BPI [15, 16].

Information on duration of the hospital stay in days, days until return to systemic oncological therapy, local control, and progression free survival and overall survival will be captured from the electronic health record. Also, occurrence of neurological deterioration, defined as deterioration of more than one grade on the American Spinal Cord Injury Association (ASIA) scale as measured by physical examination by a neurologists or trained ASIA physician, will be captured from the electronic health record [19, 20].

AEs are defined as any undesirable experience occurring to a patient during the study that may be related to the experimental treatment procedure. AEs during hospital stay will be evaluated using the most recent version of the National Cancer Institute Common Toxicity Criteria of Adverse Events (CTCAE; version 5.0, version 6.0 when available at the start of the study). AEs after hospital discharge reported spontaneously by the patient or observed by the research team will be recorded up to 3 months after treatment.

For cost-effectiveness evaluation, resource use, costs, and quality-adjusted life years (QALYs) are measured for each patient in both randomization groups over the follow-up period. Resource use such as doctor visits, medication, hospital admissions, and surgical interventions, as well as out-of-pocket expenses such as for over-the-counter drugs and travel costs, will be captured using the iMCQ at 3 and 6 months [21]. Where relevant, questionnaire responses will be verified or completed by data from the medical records. Total costs for each patient will be calculated by multiplying the resource use with unit costs. Unit costs will be calculated according to the guidelines for costing research. QALYs will be calculated from the EQ-5D-5L, using the area under the curve approach [23].

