### Objectives {7}

The primary objective of this study is to evaluate the effectiveness of SBRT followed by surgical stabilization with or without decompression within 24 h compared with the standard of care, which is surgical stabilization with or without decompression followed by radiotherapy (either cRT or SBRT) as soon as the wound is healed sufficiently, in terms of physical functioning at four weeks after the start of the treatment.

Secondary objectives are as follows:To compare the pain response, duration of pain relief, length of hospital stay, time to return to systemic oncological therapy including hormonal, immune, targeted, and chemotherapy, neurological deterioration, adverse events (AEs) such as wound complications, HRQOL, and survival between the intervention and control group, andTo study the cost-effectiveness to assess whether same-day SBRT and surgery is cost-effective compared with the standard of care, from a societal perspective.

It is hypothesized that the same-day treatment procedure will result in faster recovery of mobility, less hospital visits, earlier pain relief from irradiation, and faster restart of systemic oncological therapy without an increase in wound complications due to the short interval between surgery and radiotherapy.

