### Assignment of interventions: blinding

#### Who will be blinded {17a}

Patients randomized to the control group will not be informed about the trial and receive standard of care. Hence, patients in the control group will be blinded to group allocation. They will even be unaware of the existence of this trial. In contrast, patients randomized to the intervention group will be informed about the intervention which they can accept or refuse. It is not possible to blind researchers and clinicians for group allocation.

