#### Adverse event reporting and harms {22}

Adverse events during hospital stay will be evaluated using the most recent version of the CTCAE (version 5.0, version 6.0 when available at the start of the study). Due to the natural course of the disease, we expect that many patients with spinal metastases suffer from study unrelated AEs. Therefore, only study-related AEs with grade 2 or higher (either expected or unexpected) reported spontaneously by the patient or observed by the research team will be recorded up to three months after treatment.

Grade 3 or higher adverse events are considered serious (S) AEs. (S)AEs that are common in this patient category include urinary tract infections, delirium, pressure sores, and opioid-related adverse drug events and will be recorded but not reported to the ethics committee. Study-related SAEs within 3 months after start of treatment that are life threatening or that resulted in death will be directly reported (within 7 days) to the ethics committee. Other study-related SAEs will be reported to the ethics committee within 15 days. SAEs unrelated to the study will not be directly reported to the ethics committee but documented in the yearly progress report.

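### Adverse events are defined by possible relation to the experimental procedure, which biases the planned between-arm comparison of wound complications against the intervention arm

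*Protocol article*

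**What the plan says.** Objectives {7} lists among the outcomes to be compared "adverse events (AEs) such as wound complications, HRQOL, and survival between the intervention and control group". The hypothesis in the same section is that same-day treatment brings its benefits "without an increase in wound complications due to the short interval between surgery and radiotherapy".

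The outcome itself is defined in Plans for assessment and collection of outcomes {18a}: "AEs are defined as any undesirable experience occurring to a patient during the study that may be related to the experimental treatment procedure". The secondary outcome list in Outcomes {12} uses the same definition, so it is not a slip in one place.

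Adverse event reporting and harms {22} adds a filter for the three months after treatment: what is recorded is "only study-related AEs with grade 2 or higher (either expected or unexpected) reported spontaneously by the patient or observed by the research team". Events during the hospital stay are evaluated with the CTCAE. The same section calls grade 3 or higher events serious. It says that serious events unrelated to the study go into the yearly progress report.

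Intervention description {11a} gives standard of care to the control arm and to intervention-arm patients who refuse. Who will be blinded {17a} says of controls: "They will even be unaware of the existence of this trial". It adds that researchers and clinicians cannot be blinded.

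**The concern.** A comparison between arms needs an event definition that a patient in either arm can meet. Here an event counts only if it may be related to a procedure that controls and refusers never undergo. A wound infection after a control patient's surgery or later radiotherapy is the comparator event that the objective needs, and the definition leaves it out.

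Ascertainment pulls the same way. Relatedness is judged by staff who know the allocation. After discharge, capture depends on spontaneous report or on observation by the research team, and controls do not know that a trial is running.

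At stake is the main comparative safety question. The only earlier safety data that the article cites for surgery within 24 hours of SBRT are 13 patients in a first-in-man study, with no wound complications (Provisions for post-trial care {30}). If the stated rule is followed, an excess in the intervention arm may reflect the counting rule alone.

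**Working it through.** **Step 1: who can have a qualifying event**

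| Event | Accepts same-day treatment | Control or refuser |
|---|---|---|
| Grade 2 wound complication | Meets the definition; recorded | Not related to the experimental procedure; no stated route |
| Grade 3 or higher wound complication | Recorded as a study-related serious event | At most documented as an unrelated serious event in the yearly report |
| Common events named in section {22} | Recorded | Recorded, but the named examples do not include wound complications |

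**Step 2: arm size.** The article gives no figure for adverse events, so only the arm size comes from it. Sample size {14} uses a 13-point difference, SD 22, 80% power and two-sided 5%:

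n = 2 × (1.96 + 0.84)² × 22² / 13² ≈ 45 per arm. Then 45 / 0.9 = 50 per arm, 100 in total.

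This reproduces the stated figures, and the point does not affect them.

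**Step 3: bias in the risk difference.** Let the true risk be r in both arms, with all intervention-arm events counted and a fraction c of control events counted. The recorded difference is r − c·r = r(1 − c), although the true difference is 0. At r = 10%:
- c = 0: 5 of 50 against 0 of 50, a spurious 10 points.
- c = 0.5: a spurious 5 points.
- c = 1: no bias.

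**Step 4: chance of a false difference.** This assumes a two-sided Fisher test at 0.05 with 50 per arm. The article states no test for adverse events. With no control events, p = 2 × C(50,k) / C(100,k):
- k = 5: p = 0.056.
- k = 6: p = 0.027, so six against none is enough.

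With c = 0 the chance of a false difference is P(X ≥ 6) for X ~ Binomial(50, r). For the other rows it is the sum of binomial probabilities over all pairs of counts with p < 0.05. The article gives no complication rate for either trial arm, so the risks are assumed.

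| Control capture | r = 5% | 10% | 15% | 20% |
|---|---|---|---|---|
| None (c = 0) | 3.8% | 38% | 78% | 95% |
| Half (c = 0.5) | 1.2% | 6% | 12% | 20% |
| Same as intervention (c = 1) | 0.7% | 1.8% | 2.4% | 2.8% |

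**Step 5: refusers.** Sample size {14} expects 90% acceptance. If the 10% who refuse are analysed in the intervention arm and their events do not qualify either, the recorded intervention risk is 0.9r. The first row becomes 2.4%, 29%, 68% and 91%.

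**The case against.** Several points on the other side have force.

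- *Control events are not wholly invisible.* A reader might infer that the control arm can have no events on file. The article does not support that. Section {22} says that common events, with examples that end in "opioid-related adverse drug events and will be recorded but not reported to the ethics committee", are still written down. It also documents unrelated serious events yearly, and in-hospital events are graded with the CTCAE. The no-capture row is therefore the extreme case. What remains is the loss of grade 2 events and the lack of any stated route from the yearly report into the between-arm analysis.
- *The term study-related is open to interpretation.* Section {22} contrasts it with the natural course of the disease, which could leave complications of treatment in either arm in scope. Section {30} lists events of standard care separately, which points the other way. The ambiguity stands, but the definition in {12} and {18a} names the experimental procedure, and the qualifier that an event may be related does not bring controls in.
- *The health record could supply the events.* Section {18b} says that other secondary outcomes come from the record. Section {18a} lists the record-based outcomes, and adverse events are not among them. Extraction under the same definition would keep the same filter.
- *An analysis plan may settle it.* It can choose the analysis, but it cannot analyse events that were never collected. The definition here is stated, not left open.

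Two further inferences should be avoided. First, the time windows do not contradict each other. Sections {18a} and {22} agree on three months after treatment for recording. The phrase "Study-related SAEs within 3 months after start of treatment" governs which events go quickly to the ethics committee. Second, the article nowhere says that it would conclude no increase from a non-significant test. It states a hypothesis only.

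**Conclusion.** The point holds. The adverse event definition and the study-related filter do not fit the between-arm comparison in Objectives {7}, and following them biases that comparison towards an apparent excess in the intervention arm.

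The size depends on the true risk and on how many control events are captured in practice, and the article gives neither. At an assumed 10% risk, the chance of a false difference runs from 1.8% with equal capture through 6% with half capture to 38% with none. At 5% risk it stays below 5% even with no control capture. These figures assume equal true risk, full capture in the intervention arm and a Fisher test. The bias r(1 − c) in the risk difference needs no test.

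The primary outcome and the sample size are unaffected. So is neurological deterioration, which is taken from the health record with no relatedness condition. The defect concerns one secondary outcome, but it is the outcome that carries the safety hypothesis.

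**What to change.** For the between-arm analysis:
- Count any event of grade 2 or higher, with wound complications named explicitly, regardless of attribution.
- Use one window for all patients, from the start of first treatment to 3 months after it.
- Extract events from the electronic health record in the same way for controls, acceptors and refusers.
- Report the risk difference with its 95% confidence interval. At 10% risk in both arms the half-width is 1.96 × √(2 × 0.10 × 0.90 / 50) = 0.118, about 12 points, so readers will see how much the trial can say.

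Keep the study-related filter only for reporting to the ethics committee, and say in sections {12}, {18a} and {22} which definition serves which purpose.

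The cost is a change of wording and a modest amount of extra record extraction, mainly in controls, whose records are already used for other outcomes. Recruitment began in November 2022, but events that have already occurred can still be recovered from the records as far as they were noted there.

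### Wound complications are to be compared between arms, but the adverse event definition and recording rule depend on relation to the experimental procedure, so events can be missed unequally

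*Protocol article*

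**What the plan says.** All references are to the Protocol article.

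- **Objectives {7}** lists among the secondary comparisons "adverse events (AEs) such as wound complications, HRQOL, and survival between the intervention and control group". The hypothesis is that same-day treatment brings its benefits "without an increase in wound complications due to the short interval between surgery and radiotherapy".
- **Outcomes {12}** and **Plans for assessment and collection of outcomes {18a}** define an adverse event in the same terms, in {18a} as: "AEs are defined as any undesirable experience occurring to a patient during the study that may be related to the experimental treatment procedure".
- **{18a}** has in-hospital events evaluated with CTCAE. For later events it says: "AEs after hospital discharge reported spontaneously by the patient or observed by the research team will be recorded up to 3 months after treatment". The same section names the outcomes taken from the health record: hospital stay, time to systemic therapy, neurological deterioration, and "local control, and progression free survival and overall survival will be captured from the electronic health record". Adverse events are not on that list.
- **Adverse event reporting and harms {22}** narrows recording to "only study-related AEs with grade 2 or higher (either expected or unexpected) reported spontaneously by the patient or observed by the research team".
- **Who will be blinded {17a}** says that controls do not know the trial exists and that researchers and clinicians cannot be blinded.
- **Intervention description {11a}** gives standard care to controls and to patients who refuse the intervention. Under intention to treat ({20a}, {20c}), refusers stay in the intervention arm.

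**The concern.** A between-arm comparison needs one event definition that works in both arms. Here, whether an event counts depends on its possible relation to a procedure that only one group undergoes. A wound breakdown after standard surgery in a control patient cannot sensibly be attributed to same-day SBRT and surgery, so the rule as written does not require it to be counted.

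The relatedness filter is also applied by people who know the allocation. They could treat a wound problem after same-day treatment as an ordinary surgical event and leave it out. Under-recording in controls would make the new sequence look more harmful than it is. Under-attribution in treated patients would make it look safer. A reader of the results could not tell which had happened.

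Wound healing is the central safety question when surgery follows radiotherapy within 24 hours. The protocol's support for safety is a first-in-man study of 13 patients with no wound complications ({30}), so the randomized comparison carries real weight.

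**Working it through.** **Step 1. Which events have a stated route into the outcome?** This sets {12}, {18a} and {22} side by side.

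- *Treated intervention patient:* the event can be related to the procedure. It is recorded if it is grade 2 or higher, judged study-related, and volunteered or noticed.
- *Control patient:* there was no experimental procedure. Read literally, the event fails the definition whatever its grade.
- *Refuser:* same as a control for recording, but analysed in the intervention arm.

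CTCAE grading in hospital sets severity. It does not remove the relatedness condition.

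**Step 2. How far could recorded rates part?** The protocol gives no wound rate or capture rate, so there is no figure of its own to reproduce. Inputs:

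- 50 patients per arm (Abstract; Sample size {14}).
- 90% acceptance ({14}), giving 45 treated patients and 5 refusers in the intervention arm.
- Assumed: the same true rate *p* in everyone, full capture in treated patients, and capture *c* in controls and refusers.

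Recorded rate, intervention arm = (45*p* + 5*pc*)/50. Recorded rate, control arm = *pc*. The difference is 0.9*p*(1 − *c*).

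With *p* = 0.10:

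- *c* = 0.75: (4.5 + 0.375)/50 = 9.75% against 7.5%, a spurious excess of 2.25 points.
- *c* = 0.50: (4.5 + 0.25)/50 = 9.5% against 5.0%, a spurious excess of 4.5 points.
- *c* = 1: 10% against 10%, no excess.

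The same formula with *c* from 0.75 down to 0.50 gives an excess of about 1.1 to 2.3 points at *p* = 0.05 and about 3.4 to 6.8 points at *p* = 0.15.

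**Step 3. The opposite direction.** Assume a true rate of 20% in treated patients and 10% in refusers and controls. By allocated arm the truth is (45 × 0.20 + 5 × 0.10)/50 = 19% against 10%. If half of the treated patients' events are judged not study-related and all others are captured, the recorded rates are (45 × 0.10 + 5 × 0.10)/50 = 10% against 10%. A 9-point excess disappears.

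**The case against.** The best case against is that control events would often be picked up anyway.

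- Section {18b} says in general terms that other secondary outcomes rest on the medical record and will be nearly complete, and the list in {18a} is not called exhaustive.
- Resource use, including admissions and surgical interventions, is collected in both groups, so a wound problem that needs readmission or reoperation should leave a trace.
- Section {22} has common (serious) events recorded and puts study-unrelated serious events in the yearly progress report.
- This is a single centre, and control radiotherapy waits for the wound to heal, so treating clinicians would often see a control wound problem.

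This makes near-zero capture in controls implausible. A reader might infer that control wound complications will simply not be recorded; the documents do not support that.

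A reader might also infer a high risk of a falsely significant excess. That is not supported either, because the statistical methods section {20a} names no test for adverse events. If a two-sided Fisher test is assumed, exact enumeration with counts Bin(45, *p*) + Bin(5, *pc*) against Bin(50, *pc*) gives 2.2% at 75% capture and 5.2% at 50% when *p* = 10%, against 0.9% with equal capture. At a true rate of 5% it never exceeds 2.4%.

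The harms section words one time limit as "Study-related SAEs within 3 months after start of treatment", while recording runs to 3 months after treatment. A reader might infer different follow-up by arm, but this may be loose shorthand and does not support a separate finding. Nor does the definition imply that safety oversight is absent.

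What the objection leaves standing is the rule itself. The record sentence in {18b} does not name adverse events or lift the relatedness filter, and {18a} gives them a separate route. The yearly report is regulatory and covers grade 3 or higher, so an unrelated grade 2 wound event in a control has no stated route into the outcome. The article condenses a fuller protocol, which excuses missing detail but not a definition that it does state.

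**Conclusion.** The point holds as a conflict between the planned comparison and the stated definition and recording rule. Wound complications in controls and refusers can fall outside the outcome, and unblinded attribution can exclude events in treated patients. The comparison can therefore be biased in either direction, and neither the sign nor the size can be derived from the protocol.

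The illustrated spurious excess of 2.25 to 4.5 points rests on an assumed equal true rate of 10%, 50-75% capture in controls and refusers, full capture in treated patients, and 90% acceptance. It shows scale and is not a forecast. The primary outcome, its sample size and its type I error are untouched. Expedited reporting of serious events is not in question. The change should be made because this is the trial's main safety comparison and the remedy is cheap.

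**What to change.** In Outcomes {12}, Plans for assessment and collection of outcomes {18a} and Adverse event reporting and harms {22}, state:

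*In both arms, including patients who refuse the intervention, every wound complication of CTCAE grade 2 or higher up to 3 months after the start of treatment is recorded from the electronic health record, regardless of judged relatedness. The comparison is made by allocated arm.*

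Keep relatedness only for expedited reporting of serious events.

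The cost is a wording change in three sections and a chart check of about 100 patients, in a source already used for other outcomes. Cohort consent covers clinical data ({8}), so controls need not be contacted.

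One limit remains. Controls have their wound checked before postoperative radiotherapy and same-day patients may not, so chart data will not be perfectly symmetric. The grade 2 threshold reduces this but does not remove it.

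### Post-discharge adverse events are captured passively while only one arm knows of the trial, so the wound-complication comparison is at risk of differential ascertainment

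*Protocol article*

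**What the plan says.** All references are to the Protocol article.

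- **In hospital ({18a}):** "AEs during hospital stay will be evaluated using the most recent version of the National Cancer Institute Common Toxicity Criteria of Adverse Events".
- **After discharge ({18a}):** "AEs after hospital discharge reported spontaneously by the patient or observed by the research team will be recorded up to 3 months after treatment".
- **Harms section ({22}):** the same route, with a filter: "only study-related AEs with grade 2 or higher (either expected or unexpected) reported spontaneously by the patient or observed by the research team".
- **Definition ({18a}):** "AEs are defined as any undesirable experience occurring to a patient during the study that may be related to the experimental treatment procedure".
- **Who knows ({17a}):** of controls, "They will even be unaware of the existence of this trial"; by contrast, "patients randomized to the intervention group will be informed about the intervention which they can accept or refuse". The same section says that researchers and clinicians cannot be blinded. Under {8} and {26a}, trial-specific consent is taken from acceptors only.
- **Use of the data ({7}):** adverse events, with wound complications as the example, are compared between arms. The hypothesis is that recovery will be faster "without an increase in wound complications due to the short interval between surgery and radiotherapy".
- **Record-based outcomes:** {18a} names hospital stay, return to systemic therapy, local control, progression-free and overall survival, and neurological deterioration as taken from the electronic health record. Adverse events are not in that list. {18b}, however, says in general terms that the other secondary outcomes rest on the medical record and so will be almost complete.

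**The concern.** A post-discharge event enters the dataset only if the patient volunteers it or the team notices it. Both routes can differ by arm.

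- **Volunteering.** An acceptor has been told of a new procedure, has signed consent for it and knows that a trial team is following the result. A control has no such prompt. The Discussion argues that knowledge of allocation can change how patients rate subjective outcomes; spontaneous reporting is open to the same influence.
- **Noticing.** The observers know the allocation. Contact also differs: under {11a}, controls return after wound healing for a planning CT, a further MRI and radiotherapy, whereas acceptors had their radiotherapy before surgery.

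The randomised comparison carries most of the weight on safety. The only clinical evidence cited for the 24-hour sequence ({30} and Discussion) is a first-in-man study of 13 patients without wound complications. If capture differs by arm, an excess or an absence of wound events could not be separated from who was prompted to report and who was seen.

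**Working it through.** **1. Is another source laid down for these events?**

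| Section | What it provides | Does it settle the source of post-discharge events? |
|---|---|---|
| {18a}, {22} | Spontaneous report or team observation | Yes, explicitly and twice |
| {18a}, record-based outcomes | Named list | Adverse events not on it |
| {18b} | Other secondary outcomes rest on the record | Points the other way, but does not name adverse events |
| {18a}, questionnaires | C15-PAL, BM22, EQ-5D-5L, BPI | No wound or event checklist described |
| {18a}, iMCQ at 3 and 6 months | Admissions and surgery, both arms | Collected for costs, not designated a safety source |
| {11c}, {18b}, phone calls | Questionnaire reminders and primary-outcome items | No question on events described |
| {21a}, monitor | Consent, procedures, data accuracy | No ascertainment of events by arm |

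The specific rule is passive. The only text pointing elsewhere is the general sentence in {18b}.

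**2. The plan's own figures.** The protocol gives no expected event rate, so there is none to reproduce. The number per arm comes from {14}: n = 2 × (1.960 + 0.842)² × 22² / 13² = 44.96, that is 45 per arm, and 45 / 0.90 = 50. This agrees with the plan and is used below only as the denominator.

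**3. How much unequal capture could matter (assumed values).** Observed risk = true risk × probability of capture. With the same true risk in both arms, the apparent risk ratio is the ratio of the capture probabilities:

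- 90% v 90%: 1.00
- 90% v 70%: 0.90 / 0.70 = 1.29 (reversed, 0.78)
- 90% v 50%: 0.90 / 0.50 = 1.80 (reversed, 0.56)

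With 50 per arm, exact two-sided Fisher test at 5%, and the higher capture (90%) in the intervention arm:

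| True risk, both arms | Control capture | Observed risks | Spurious difference | Chance of p ≤ 0.05 |
|---|---|---|---|---|
| 10% | 90% | 9.0% v 9.0% | 0 | 1.6% |
| 10% | 70% | 9.0% v 7.0% | 2 points | 2.1% |
| 10% | 50% | 9.0% v 5.0% | 4 points | 4.3% |
| 20% | 90% | 18.0% v 18.0% | 0 | 2.7% |
| 20% | 70% | 18.0% v 14.0% | 4 points | 4.7% |
| 20% | 50% | 18.0% v 10.0% | 8 points | 12.9% |

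At a true 20%, the middle case is 50 × 0.18 = 9 events against 50 × 0.14 = 7.

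**4. The opposite direction.** Suppose the true risks are 20% (intervention) and 10% (control), with capture of 50% and 90%. The observed risks are 0.20 × 0.50 = 10% and 0.10 × 0.90 = 9%. A true doubling shows as a ratio of 1.11.

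**5. What the comparison can carry.** For 0 events in 13 patients, the exact two-sided 95% upper limit is 1 − 0.025^(1/13) = 24.7%, so the earlier study leaves much open. With 50 per arm, power to detect 20% v 10% is about 19% (Fisher) to 29% (normal approximation).

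**The case against.** The case on the other side is substantial.

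- **The record may already be the source.** Adverse events are a listed secondary outcome and not a questionnaire score, so the sentence in {18b} can be read to include them, and the team may observe an event through the chart. This stands in part: record review is not ruled out. It does not remove the point, because {18a} and {22} give adverse events their own rule, and a general sentence on retention does not override it. If record review is intended, the sections need to be reconciled.
- **Much contact is the same in both arms.** Controls consented to the cohort, questionnaires and reminder calls make no distinction by arm, and the iMCQ covers admissions and surgery for everyone. This stands, and it narrows the concern.
- **A patient with a wound problem contacts the hospital, trial or no trial.** At a single centre, severe events would probably be seen in either arm. This stands too. What remains is mainly grade 2 events, but {22} makes grade 2 the threshold for recording, so they count.
- **The comparison is secondary and has little power.** True under any method of capture. Low power calls for caution in interpretation; it does not make unequal capture harmless.

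A reader might infer that the wound-complication comparison is biased, or biased against the intervention. The documents do not support that. Unaware controls may report less, which would exaggerate harm; their extra visits may lead to more being seen, which would mask it; unblinded judgement could act either way. {11a} describes no surgical follow-up for either arm, so net contact is unknown.

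**Conclusion.** The point holds as a risk. Followed as written, the rule for post-discharge events lets ascertainment differ between an arm that largely knows of the trial and an arm that does not, for a comparison the protocol intends to make. The exposure is mainly to grade 2 events. Size and direction are unknown: the true risks and capture probabilities in the working are assumptions, and they show only that moderate differences in capture could produce apparent risk ratios of about 1.3 to 1.8, or the reverse, with no true difference. It should be corrected before adverse events are compared between arms. It does not touch the primary outcome.

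The definition of an adverse event, tied to the experimental procedure, is a related weakness: a control's wound complication may not qualify at all. Rewording the definition alone would leave the reporting route unequal.

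**What to change.** Reconcile {18a} and {22} with {18b} by naming one source for the between-arm comparison:

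- a structured review of the health record for every randomised patient in both arms, whether or not anyone reported an event;
- one checklist worded without reference to allocation: wound infection, dehiscence, reoperation, readmission, and other CTCAE events of grade 2 or higher;
- one fixed window in both arms, 3 months from start of treatment;
- a cross-check against the admissions and surgery items of the iMCQ at 3 months, already collected in both arms.

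Keep spontaneous reports for expedited safety reporting, outside the arm comparison.

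The cost is abstraction time for 100 patients at one centre, from records already used for other outcomes. Controls stay uninformed and no treatment changes. Two limits remain. Milder events managed outside the hospital will be missed. And the review reduces the imbalance without removing it, because controls' additional post-operative radiotherapy visits also create chart entries; this should be acknowledged when the comparison is interpreted.
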